Other secondary endpoints will include side effects attributable to IVIG, trough levels of IgG, acute rejection episodes, FEV1%, FVC%, incidence of bronchiolitis obliterans syndrome, and mortality. **All of these tests are obtained as part of routine clinical care of the lung transplant recipient.**

At each drug or placebo administration, patients will be questioned regarding potential endpoints in the interim since their last visit. Potential endpoints will be identified by any symptoms, antibiotic use, or contact with either the transplant team or outside physicians. Patients will be examined during each infusion and a specially-trained nurse will assess vital signs and side effects during infusions.

At the conclusion of the study period, the medical records from all potential endpoints will be reviewed by a consensus panel of three physicians who are blinded to the treatment assignment and subject identity. They will review the potential endpoints using our explicit guidelines.

Assessment of Phagocytic Function

Peripheral blood (20ccs) will be obtained by venipuncture; mononuclear cells will be isolated by density centrifugation and monocytes will be purified from this fraction by adherence to tissue culture plastic in the presence of 20% human serum. In our hands this results in a purity of >90% monocytes. Following an overnight incubation, cells will be replated onto glass coverslips and maintained in a 5% CO2 incubator at 37ºC for 5 days to allow for differentiation into macrophages. Standard phagocytosis assays will be performed in triplicate using 107 colonies of P. aeruginosa (strain PAO1), methicillin-sensitive S. aureus (ATCC 29213) or a virulent capsular type 2 strain (D39) of S. pneumoniae. These strains were chosen as representative of the majority of bacterial infections that have been documented in primary HGG and in our lung transplant patients with severe HGG. Phagocytosis assays will be performed in the presence of 50% autologous serum and in the absence or presence of 10 mg/ml supplemental pooled human IgG. In addition, whole blood bactericidal assays will be performed as described. Parallel assays will be performed in the presence of supplemental pooled human IgG (10 mg/ml), which will serve as a control for the optimal magnitude of IgG-dependent phagocytosis and killing. All phagocytosis and whole-blood bactericidal assays will be performed in the laboratory of [name].

4. Study Drug

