IVIG is a pooled plasma product that was FDA-approved for use in primary immunodeficiency syndromes in 1981. IVIG is also widely used in secondary immunodeficiency states, such as HIV infection, bone marrow transplantation, leukemia, and other disorders. We will use immune globulin intravenous (Human), 10% Caprylate/Chromatolgraphy Purified (Gamunex) (Bayer, Elkhart, IN) for this protocol. This preparation was selected based on the lower incidence of renal dysfunction with this product. The plasma source is over 2000 paid human donors. The in vivo half-life is approximately 35 days. IgG constitutes 95-99% of the fractionated serum with only traces of IgA, IgM, IgD and IgE. The usual maintenance dose is 300-600 mg/kg every 3 to 4 weeks, which reduces the incidence and severity of infections in primary immunodeficiencies. The dose of IVIG in this study will be 400 mg/kg every 4 weeks, which is the most widely utilized dosage in clinical practice. The initial infusion rate will be 0.01 mL/kg minute which will be titrated to a maximum infusion rate of 0.08 mL/kg/min. IVIG therapy is generally well-tolerated, with a 5% incidence of side effects. These include fever, chills, headache, back pain, chest pain, malaise, myalgia, nausea, vomiting, and rash. Most of these reactions are mild and self-limited, and often can be alleviated by reducing the rate of infusion. Major adverse reactions occur very infrequently, including a hypersensitivity reaction with anaphylaxis (mainly in IgA-deficient patients, who will be excluded), aseptic meningitis and nephrotoxicity. The transmission of HIV or hepatitis B with currently available products has not been reported. Early reports of hepatitis C transmission with the use of IVIG have led to significant changes in the manufacturing process, resulting in no recent reports of seroconversion. Placebo will be 0.1% Albumin in an equal volume, prepared by the Columbia Research Pharmacy. All patients will be pre-medicated with acetaminophen 650 mg po and diphenhydramine 25 mg po before the study drug infusion.

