The Research Pharmacy at Columbia University will randomly assign treatment order. Investigators, study personnel, and patients will be blinded to the order and identity of the treatments. The immunoglobulin/placebo will be prepared by an unblinded Research Pharmacist and delivered to the infusion suite. The infusion protocols will be identical between placebo and active drug. The study drug/placebo will be administered in the infusion suite of the Beverly & Arthur Shorin Transplant Center.

5. Study Questionnaires

N/A

6. Study Subjects

Study Population

The subjects for this protocol will be 10 lung transplant recipients who are patients at the Columbia University Medical Center (CUMC) Lung Transplantation Program who were transplanted more than 3 months prior to recruitment. As the majority of changes in immunosuppressive therapy occur in the first 3 months following lung transplantation, patients will receive a stable immunosuppressive regimen at the end of this period. Additionally, HGG is not expected to occur within the first 3 months after transplantation and is typically observed after 6 months. **All patients are currently screened by quantitative serum immunoglobulin (IgG, IgA and IgM) assay as per the clinical protocol of the Lung Transplant Protocol of Columbia University.** **This is a routine procedure in the clinical care of transplant patients at our center.** Patients who are identified to have severe HGG (as defined by serum IgG levels less than 400 mg/dL) will be eligible for the crossover study. Eligible patients will be identified by the Key Personnel who comprise the CUMC Lung Transplant Team. **As is common in the study of rare diseases, the clinicians who are caring for the patients will recruit and consent patients for the study. Patients will be assured that their participation or lack thereof will not affect their clinical care.**

Inclusion criteria:

Lung transplant recipients > 3 months after transplant surgery

IgG < 400 mg/dL on two assessments at least one month apart within three months

Stable medical regimen for one month before enrollment

Exclusion criteria:

Acute rejection episode as defined histologically by the Lung Rejection Study Group within one month before enrollment

Active infection within one month of enrollment

Contraindication to IVIG (Acute renal failure, severe selective IgA deficiency, known hypersensitivity to IVIG)

Pregnancy

Recent (less than 3 months) history of thrombotic events

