Because of the possibility (albeit small) of a major adverse effect, IVIG or placebo will be administered with manufacturer-recommended infusion rates and monitored in the infusion suit of the Lung Transplant Center, which has extensive experience in infusion of IVIG and other intravenous therapies. The transmission of HIV or hepatitis B with currently available products has not been reported.

We will institute strict procedures to minimize the risks to the participants in this study. Blood sampling will be performed by trained phlebotomists. IVIG has been studied extensively in both normals and in patients with primary and secondary HGG and after bone marrow transplantation and is FDA-approved. Although IVIG has not been studied in patients after solid organ transplantation, it is expected that the side effects of the study infusion will be similar to these other populations. We will have specially-trained infusion nurses supervise all IVIG and placebo infusions. The nurses will have standardized protocols for responding to side effects with alteration in infusion rates or cessation of infusions with severe adverse events. Subjects will be examined by a physician at each study visit. We will use Gamunex which has a lower risk of nephrotoxicity than other IVIG preparations.

10. Potential Benefits

There may be no direct benefits. The results from the study could be applied in the future to patients (including those in the study) who stand to benefit from the information. As future studies of HGG may emerge from this study, there may be significant benefit for patients with HGG (including those in this trial). As the study involves the risks of phlebotomy and administration of IVIG, and there is a potential for future benefit for both subjects in the study and for future patients, the risk/benefit ratio is favorable.

The knowledge to be gained from this study is potentially very important. The clinical impact of HGG and the effect of IVIG is unknown. To our knowledge, there are no published studies examining the effects of IVIG in this patient population. In order to proceed with a definitive clinical trial, we must establish “proof of principle”. As the risks to the subjects of this protocol are low, i.e. phlebotomy and administration of IVIG, there is a favorable risk/benefit ratio considering the importance of performing research in this area.

11. Alternatives

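### The side-effect endpoint is conditioned on attribution to IVIG, so as worded it does not use the placebo comparison that the crossover provides

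*Protocol*

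**What the plan says.** The protocol's list of secondary endpoints (section 3, Study Procedures) includes: "Other secondary endpoints will include side effects attributable to IVIG". It does not say who makes the attribution, when, or how an event in a placebo period is scored.

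Blinding is broad. Sections 3 and 4 state: "Investigators, study personnel, and patients will be blinded to the order and identity of the treatments". Only the research pharmacist who prepares the infusion is described as unblinded. Potential endpoints go to "a consensus panel of three physicians who are blinded to the treatment assignment and subject identity" (section 3).

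The provisions for collecting the data carry no attribution condition:

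- Section 3: "a specially-trained nurse will assess vital signs and side effects during infusions".
- Section 3: "At each drug or placebo administration, patients will be questioned regarding potential endpoints in the interim since their last visit". Any symptom is enough to flag a potential endpoint.
- Section 4: "The infusion protocols will be identical between placebo and active drug".
- Section 9: "We will have specially-trained infusion nurses supervise all IVIG and placebo infusions". The same section has a physician examine subjects at each study visit.

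Section 4 puts the incidence of side effects with IVIG at 5% and names "aseptic meningitis and nephrotoxicity" among the rare major reactions. Infusions are given at weeks 0, 4 and 8 and at weeks 24, 28 and 32. Weeks 12 and 36 are assessment visits without an infusion.

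**The concern.** In a placebo-controlled crossover, the comparison of IVIG with placebo in the same patient is what shows whether IVIG causes an effect. An endpoint that requires attribution before an event counts puts an individual judgement in place of that comparison. Here the judgement is hard to make, for three reasons found in the protocol itself.

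- **Blinding.** A blinded rater can judge whether an event looks related to the infusion just given, but cannot know that the infusion was IVIG.
- **Background events.** Section 1 says that infection prophylaxis in these patients already causes renal and allergic toxicity, which overlaps with the major reactions listed for IVIG in section 4. Several of the minor reactions listed there, such as fever and chills, can also accompany infection, which is the primary outcome.
- **No earlier experience.** Section 9 says that IVIG has not been studied after solid organ transplantation. Attribution guided by the known profile would tend to drop harms peculiar to this population.

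Section 1 also hopes that IVIG will let prophylaxis be reduced, with less drug toxicity. An endpoint restricted to events attributed to IVIG could not show such a benefit.

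At stake is whether the side-effect result of this pilot can be read as a comparison of IVIG with placebo.

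**Working it through.** **The plan's figures.** The protocol gives no sample size or target for the safety endpoint. Its 10 subjects come from a one-standard-deviation reduction in bacterial pneumonias. That figure reproduces: a paired t-test with two-sided alpha 0.05 and a difference of one standard deviation of the within-patient differences has power 0.803 at n = 10 (0.748 at n = 9). It does not bear on this point. The only relevant figure is the 5% side-effect incidence in section 4, which has no stated denominator, so both readings are shown.

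**Expected events in the IVIG periods** (events treated as independent):

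| Reading of 5% | Units | Expected events | Chance of at least one |
|---|---|---|---|
| Per patient | 10 | 10 × 0.05 = 0.5 | 1 − 0.95^10 = 0.40 |
| Per infusion | 10 × 3 = 30 | 30 × 0.05 = 1.5 | 1 − 0.95^30 = 0.79 |

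On either reading, including or excluding a single event changes the result materially.

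**Effect of an attribution filter.** Let the true rates be q1 under IVIG and q0 under placebo, and let a blinded filter keep the same share s of events in both periods. The ratio is (s·q1)/(s·q0) = q1/q0, which is unchanged. The difference is s·(q1 − q0), which shrinks. With assumed rates of 10% and 5% (illustration only):

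| Share kept, s | IVIG | Placebo | Ratio | Difference (points) |
|---|---|---|---|---|
| 1.0 | 10.0% | 5.0% | 2.0 | 5.0 |
| 0.7 | 7.0% | 3.5% | 2.0 | 3.5 |
| 0.5 | 5.0% | 2.5% | 2.0 | 2.5 |

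An even-handed blinded filter therefore discards events and weakens the contrast, but does not remove it. If attribution is instead read literally, with the assignment known, the placebo count is zero by definition and nothing is left to compare.

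**Timing of questioning.** Section 3 ties the interim questions to administrations:

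- After the infusions at weeks 0, 4, 24 and 28, the next questioning is 4 weeks later.
- After the week 8 infusion, it is at week 24, which is 24 − 8 = 16 weeks later.
- After the week 32 infusion, none is specified.

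The last infusion of each period is thus followed up differently from the first two, and differently between the periods, although visits at weeks 12 and 36 are already planned.

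**The case against.** The strongest case against is that the phrase is loose but does little harm. Collection is unfiltered and the same under both infusions, so the data for a period-by-period table should exist. The phrase can also be read as the class of known IVIG reactions listed in section 4, which can be counted under either treatment. Rejection, lung function, bronchiolitis obliterans syndrome, mortality and hospital admissions carry no attribution condition. Safety tabulations are often left to an analysis plan, which is not shown here. And 10 patients give no firm safety contrast under any wording.

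Much of this stands, and it rules out several stronger claims that a reader might infer:

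- **That the controlled safety comparison is lost.** It would be lost only if attribution were made after unblinding or if only attributed events were kept. The protocol says neither.
- **That blinded infusion staff are made to guess the treatment, which then affects the reporting of infections.** No passage asks a nurse or investigator for a causality judgement. The only stated review of potential endpoints is by the blinded panel.
- **That side effects are looked for only during infusions.** Interim questioning covers any symptom, and a physician examines subjects at each study visit.
- **That safety is one of the trial's aims.** The two Specific Aims concern infections and phagocytosis. Evidence of safety appears only in the rationale.
- **That renal harm goes unmeasured.** No renal measure is named among the endpoints, but section 3 takes endpoint data from routine care, so results may be available.

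Two things remain. The endpoint definition is text in this protocol, not a detail left open. And the milder reading, the class of known reactions, still leaves out unexpected events in a population in which the protocol says IVIG has not been studied.

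**Conclusion.** The point holds as a defect in the wording of a secondary endpoint. As defined, the endpoint depends on something that blinded raters cannot know, and on a literal reading it cannot occur under placebo. The unfiltered data collected under both infusions would support a controlled comparison, but the endpoint does not call for one.

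The size is modest. This is a secondary endpoint in a 10-patient pilot, with 0.5 or 1.5 events expected under IVIG depending on the unstated denominator of the 5%. How far the contrast shrinks depends on the share of events that a filter would keep, which is unknown. The 10% and 5% rates used above are assumptions. The point does not depend on any of these figures: it follows from setting the endpoint wording beside the blinding provisions. It is worth making because the correction is cheap.

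**What to change.** 1. Redefine the endpoint as all adverse events with onset from each infusion until the next study visit, in both treatment periods and regardless of judged cause, compared between IVIG and placebo within patient. This gives windows of weeks 0–4, 4–8 and 8–12, and of weeks 24–28, 28–32 and 32–36: three windows of equal length under each treatment.
2. Keep relatedness to the study infusion, judged while blinded, as a descriptive column that does not decide whether an event is counted.
3. Ask the same interim questions at the week 12 and week 36 visits, so that events after the last infusion of each period are captured in the same way as the others.
4. Where creatinine is available from routine care, tabulate it by treatment period.

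The cost is a change of endpoint wording, a set of questions at two visits already planned, and a longer listing. No visit, test or treatment is added. The downside is more background events in the table. With 10 patients the comparison should be presented as descriptive.

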Despite these potential benefits, IVIG is relatively difficult to administer (requiring monthly intravenous infusion), has potential adverse reactions, and is very expensive (> $12,000/year/patient). To date, randomized controlled trials in a solid organ transplant population have not been published. While the transplant research community is aggressively pursuing immunotolerance to enhance graft and patient survival, this concept is at least several years away for clinical transplantation. We therefore propose a pilot study of an established therapy which could be implemented today, given evidence of its safety and efficacy. Considering the suboptimal survival rates and the impact of infections in lung transplant recipients, HGG may be a treatable vulnerability in the complicated post-operative course after lung transplantation. With its ability to augment immunity to pathogenic organisms without increasing the risk of rejection, IVIG therapy could be a significant advance in post-transplant management of lung and other solid organ transplant recipients.

2. Study Design and Statistical Procedures

We will perform a Phase II double-blind, two-period, two treatment, placebo-controlled crossover trial of IVIG therapy. A cross-over design is attractive for its reduced variance and subsequent reduced sample size requirements due to within-subject comparisons. As underlying clinical stability is an essential assumption of this study design, we will select patients who are farther from transplant and have shown stability in their immunosuppressive regimens. Previous crossover trials of IVIG have established a 3 month wash-out period as sufficient to avoid a carry-over effect.

We will perform the analysis by intention-to-treat. For Specific Aim 1, the number of bacterial infections per patient will be compared between the treatment and control periods. In addition, the number of non-bacterial and total infections will be compared between the periods. If the continuous data do not meet the assumption of normality, they will be transformed, as needed. For Specific Aim 2, the number of bacteria either bound to or ingested by 100 macrophages from each subject during the treatment and control periods will be compared.

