The main method of analysis will be the linear mixed-effects model. The outcome variables will be the number of bacterial infections (Aim 1) and the phagocytosis indices and the extent of bacterial killing (Aim 2). The predictor of interest will be the treatment (IVIG or placebo). Period number will be included as a covariate. The correlation between outcomes from the same subject will be modeled using a random subject-specific intercept term. The interactions between treatment and presence of chronic rejection will be examined. Interactions between period and treatment will also be examined. Analysis of time-to-infection in each period will also be performed using proportional hazards modeling adapted for the crossover study design. The variables included in the final models will be chosen on the basis of the statistical significance of estimates, the effect of their inclusion on other factors in the model, and on scientific plausibility. Analyses will also include trough immunoglobulin levels. Tests for trends over time will be performed using the baseline measurements of IgG levels. Binary outcomes will be analyzed using appropriate methods.

Sample Size

The Lung Transplantation Center currently cares for approximately 100 patients who are beyond 3 months of their transplantation procedure, and we perform approximately 25 transplants/year. We anticipate 14% of these patients to have severe HGG. Over a recruitment period of one year, we therefore anticipate 3 new patients with severe HGG, in addition to at least 14 prevalent cases (100 post-transplant patients alive at start of recruitment x 14% severe HGG). Of these 17 patients, we expect more than 80% to meet inclusion criteria and less than 10% to refuse to participate. As lung transplant recipients have an uncommon and serious medical condition requiring multiple medications, procedures, and hospitalizations, they are particularly eager to participate in clinical trials focused on improving clinical outcomes. We have found similar refusal rates in other studies of patients undergoing lung transplantation.

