7. Recruitment

The investigators on this study are the physicians who provide all medical care for the potentially eligible subjects (lung transplant recipients at Columbia). The investigators will approach potentially eligible patients.

8. Confidentiality of Study Data

We will have several mechanisms in place to maintain confidentiality. Patient names will not be abstracted and all of the data will be reported in aggregate. Each subject in all phases of the study will be assigned a unique study code number to be used on all data forms and samples. A list of patient names and code numbers will be maintained separately in locked file cabinets or on password protected computers at the recruiting centers and centrally by the PI. Only the investigators and project staff will have access to this information. No other personally identifiable information will be available. The sponsor may have access to data which have been de-identified except for the study code number.

9. Potential Risks

We will obtain repeated blood samples from each subject. There is a risk of bruising, hematoma, and infection after phlebotomy, which are possible but not considered serious adverse events. Fainting may occur which is unlikely, but considered a serious adverse event.

Administration of IVIG is a potential risk. IVIG therapy is widely used and has become the current standard in clinical practice for replacement therapy in patients with primary and certain secondary immunodeficiency states. Presently, IVIG is FDA-approved for treatment of primary humoral immunodeficiency, Kawasaki syndrome, chronic lymphocytic leukemia and bone marrow transplant recipients with recurrent infections, and idiopathic thrombocytopenic purpura. IVIG therapy is generally well-tolerated, with a 5% incidence of side effects. These include fever, chills, headache, back pain, chest pain, malaise, myalgia, nausea, vomiting, and rash. Most of these reactions are mild and self-limited, and often can be alleviated by reducing the rate of infusion. Major adverse reactions occur very infrequently, including a hypersensitivity reaction with anaphylaxis (mainly in IgA-deficient patients, who will be excluded from the protocol), aseptic meningitis and nephrotoxicity.

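### The IgA exclusion in Section 6 is limited to the selective form, which the IgG entry criterion leaves nearly empty, so it does not deliver the exclusion stated in Sections 4 and 9

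*Protocol*

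**What the plan says.** Section 4 (Study Drug) lists anaphylaxis among the rare major reactions to IVIG and says that it occurs "mainly in IgA-deficient patients, who will be excluded". Section 9 (Potential Risks) repeats the point: "mainly in IgA-deficient patients, who will be excluded from the protocol". Neither sentence limits the exclusion by severity or by type of deficiency.

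The operative list is in Section 6 (Study Subjects, Exclusion criteria). Its only mention of IgA is inside the entry "Contraindication to IVIG (Acute renal failure, severe selective IgA deficiency, known hypersensitivity to IVIG". The bracket has no wording to mark its contents as examples, no other criterion mentions IgA, and no IgA cut-off is given.

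Two other statements in Section 6 bear on this. The inclusion criteria require "IgG < 400 mg/dL on two assessments at least one month apart within three months". The Study Population text says "All patients are currently screened by quantitative serum immunoglobulin (IgG, IgA and IgM) assay", so an IgA result is available before enrolment.

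**The concern.** The safety text states a broad exclusion and the eligibility list applies a narrower one. The list adds two qualifiers, *severe* and *selective*. The second matters more, because the trial recruits only patients whose IgG is already low. A criterion that presupposes preserved IgG fits a different population.

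At stake is whether the stated protection against the first major reaction that Sections 4 and 9 name is actually applied at enrolment. The design is a "two-period, two treatment, placebo-controlled crossover trial of IVIG therapy", so everyone who completes both periods receives IVIG. Under Section 3 that means three infusions, at Weeks 0, 4 and 8 or at Weeks 24, 28 and 32. Treatment order changes when a patient is exposed, not whether.

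**Working it through.** No figure in the protocol depends on this point, so there is nothing to recompute. The check compares every mention of IgA that bears on eligibility and runs the possible patient profiles through each text.

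Inputs:
- Sections 4 and 9: IgA-deficient patients are excluded, with no qualifier.
- Section 6, exclusion: severe selective IgA deficiency.
- Section 6, inclusion: IgG below 400 mg/dL on two assessments.
- Assumption: the protocol does not define *selective*. It is taken in its ordinary sense, IgA low while the other immunoglobulin classes are preserved.

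| Profile | Meets IgG inclusion? | Excluded by Sections 4 and 9 as worded? | Exclusion required by Section 6 list? |
|---|---|---|---|
| IgG preserved, IgA severely low | No | Yes | Yes, but cannot enter anyway |
| IgG < 400, IgA normal | Yes | No | No |
| IgG < 400, IgA mildly low | Yes | Yes | No |
| IgG < 400, IgA severely low | Yes | Yes | No, not selective |
| IgG < 400 now, selective IgA deficiency diagnosed earlier | Yes | Yes | Possibly, on history |

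The first row is the patient whom the criterion describes most naturally, and the IgG requirement already keeps that patient out. Among patients who can enter, only the last row might be caught. It is conceivable because Section 6 says that "HGG is not expected to occur within the first 3 months after transplantation and is typically observed after 6 months", which leaves room for an IgA diagnosis made while IgG was still preserved. Otherwise the criterion has almost nothing to act on.

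The fourth row is the gap. That patient satisfies the inclusion criteria, belongs to the group that Sections 4 and 9 say is excluded, and is not required to be excluded by the list. The third row is also a mismatch, but only over severity.

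**The case against.** The strongest answer is that the three texts are meant to be read together. Sections 4 and 9 mention IgA in passing while describing adverse reactions, and a risk paragraph may use a short term for a criterion set out in full elsewhere. A team that measures IgA in everyone and names IgA deficiency as the anaphylaxis risk probably meant marked IgA deficiency. The words *contraindication to IVIG* may also let the treating physician keep such a patient out, and Section 7 says that the investigators are those physicians.

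Part of this stands. Shorthand explains why *severe* is absent from Sections 4 and 9, and clinical judgement may well close the gap in practice. But shorthand does not explain *selective*, which changes the kind of patient described and does not fit the entry criterion. If the authors meant marked IgA deficiency of any kind, the word is a slip and removing it states their intention. Discretion is also weaker than the categorical exclusion stated twice elsewhere, and the criterion is not tied to the IgA result.

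Other safeguards also stand. According to Sections 4, 6 and 9, the product has only traces of IgA, infusions are titrated and premedicated, trained nurses supervise them under protocols for slowing or stopping, and known hypersensitivity to IVIG is excluded separately. These reduce the consequence without reconciling the text.

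**Conclusion.** The inconsistency is real and minor. The Section 6 criterion is nearly empty in this population and does not require exclusion of a patient with severe IgA deficiency alongside low IgG. This rests on the ordinary meaning of *selective*, which the protocol leaves undefined. Endpoints, analysis and power are unaffected.

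A reader might infer more, in three ways that the document does not support.
- *That at-risk patients will be enrolled and harmed.* The protocol gives no IgA distribution, so the number affected is unknown and could be zero, and no reaction rate can be derived for them.
- *That every degree of IgA deficiency must be excluded.* The bare wording of Sections 4 and 9 reads that way, but loose phrasing in the risk text is an adequate explanation for the missing severity qualifier.
- *That correcting the criterion would endanger recruitment.* The Sample Size text says "Of these 17 patients, we expect more than 80% to meet inclusion criteria and less than 10% to refuse to participate". These are bounds on overall eligibility and refusal and say nothing about IgA. The share meeting the criteria may already allow for contraindications to IVIG, so the loss cannot be worked out from them.

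**What to change.** In Section 6, replace the IgA item with: severe IgA deficiency on the routine screening IgA assay, whatever the IgG level. The clinical team sets the cut-off. In Sections 4 and 9, use the same term, so that all three places state one rule.

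The cost is three short wording edits and no new test, since IgA is already assayed. The downside is possibly a few fewer eligible patients, a number that the protocol does not allow to be estimated.

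If the sponsor deliberately wants only the selective form excluded, narrowing Sections 4 and 9 to match would remove the contradiction at no cost in patients. It would change nothing that the trial does, however, and would leave the criterion nearly empty, so it is the weaker remedy.
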